### Recruitment {15}

Participants will be recruited primarily by advertisements on social media. In addition, junior and senior high schools as well as healthcare providers, youth clubs, social workers and similar organizations will be contacted with information about the study. User organizations will be involved in informing such organizations about the study and recruiting participants.

## Assignment of interventions: allocation

### Sequence generation {16a}

Eligible participants will be randomized to one of the two arms (1:1 ratio). An independent researcher who is not involved in the study will conduct the randomization procedure via a computerized random number service (random.org). Randomization will be done in blocks of various sizes pending on the amount of adololescents found eligible at each inclusion conference during the project reqruitment period.

### Concealment mechanism {16b}

Randomization takes place after the participants have been found eligible through screening and subsequent diagnostic interviews, have been invited to participate in the study and confirmed their informed decision to participate. Subsequently, an independent researcher who only has access to a list of anonymous ID codes conducts the randomization. Thus, the randomization is conducted after completion of all baseline measures and final enrolment. The randomization is conducted in two steps. First, the independent researcher randomizes the two conditions IPDT and ICBT to decide what treatment should be allocated to participants on the first half of the list and what treatment should be allocated to participants on the second half of the list. Second, the anonymous ID codes are randomized, leading to a randomization list.

### Implementation {16c}

Allocation sequence is generated by the independent researcher through randomization. This will subsequently be sent to the PI, deputy PI and all project coordinators. Project coordinators will then assign the participants to interventions in accordance to the randomization list. Within hours of randomization, the study therapists are informed who will be treating which participant. The treatment begins the following day.

## Assignment of interventions: blinding

### Who will be blinded {17a}

Due to the nature of psychological treatment trials, neither participants nor therapists can be blind to treatment allocation, and all the outcome measures are self-rating scales, thereby rendering the blinding of assessors irrelevant. Prior to randomization, eligible participants are informed that they will be randomized to one out of two treatments, but information about the treatments is limited to format such as duration, structure (i.e. reading texts, therapist support via messages and chat sessions, the guided self-help format), and the hypothesis of the trial, i.e. that the treatments do not differ in effect for depression. Any acronyms or further characteristics of the specific treatments are avoided, in order to avoid expectancy effects related to prior knowledge or assumptions regarding specific treatments after randomization.

For the statistical analysis, groups will be masked meaning that the data analysts will be blinded. This means that two non-inferiority tests will be run, comparing each group’s non-inferiority towards the other, but only the one assessing non-inferiority for IPDT against ICBT will be retained.

### Procedure for unblinding if needed {17b}

Not applicable. The participants’ allocation to intervention is not blinded for the study therapists, the project coordinators or the PI.

## Data collection and management

### Outcomes {12}

The primary outcome will be severity of depressive symptoms, defined as the difference between groups in estimated change in depressive severity from baseline to end of treatment (10 weeks). Secondary outcomes will be anxiety symptoms, emotion regulation and self-compassion at treatment termination. In addition, long-term outcome in depressive and anxiety symtoms is measured at follow-up up to 1 year after termination. See the section “Data collection and management” below for details about the instruments used for measuring these outcomes.

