#### Primary research question/primary outcome

Is IPDT non-inferior to ICBT in reducing depressive symptoms from pre-treatment to end of treatment in adolescents?

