### Sample size {14}

In order to assess non-inferiority and superiority using a repeated-measures design, power calculations for two-level LMMs were made following Galbraith and Marschner [29] using the R-package powerlmm v. 0.4. A non-inferiority bound of *d* = 0.30 was set alongside an α at 0.05, a variance ratio of 0.75, an attrition rate of 20% and intermittent missing data on weekly measures of 20%. Based on these calculations, a total sample size of 270 is needed to reach 80% power. The power analysis is based on data from the pilot trial [23]. The non-inferiority margin was based on earlier non-inferiority studies comparing face-to-face PDT to CBT in adults suffering from depression, in which Cohen’s *d* = 0.30 was considered as a minimal clinically meaningful difference. Driessen et al. [30] defined non-inferiority as Cohen’s *d* = 0.30 for all continuous outcome measures. Connolly Gibbons et al. [31] defined non-inferiority as 2.5 points on the Hamilton Depression Rating Scale, which was equivalent to a Cohen’s *d* of 0.29.

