## Statistical methods

### Statistical methods for primary and secondary outcomes {20a}

Statistical reporting will follow the CONSORT standards [49]. All participants who are randomly assigned to a condition shall be entered into the main analysis (intent-to-treat analysis = ITT) of the primary outcome measure (QIDS-A17-SR) at the primary assessment point of treatment termination (10 weeks). A secondary analysis of the primary outcome measure will include a per-protocol analysis.

In order to fully explore trajectories of change, a multilevel growth curve level strategy [50] will be employed for measures assessed weekly, comparing estimated change in depressive symptom severity from baseline to end of treatment between groups. Differences in efficacy between conditions will be investigated by modelling interaction effects of group and time. These methods have been recommended for RCTs that investigate Internet interventions [51]. One important advantage is their ability to handle missing data using a maximum likelihood estimation [52]. Non-inferiority will be defined as fulfilled when the upper 90% confidence interval of the estimated QIDS-A17-SR for the IPDT group at treatment termination is below the estimate for the ICBT group plus *d* = 0.30 (i.e. the non-inferiority margin).

The number of patients who changed reliably, as estimated by the Reliable Change Index (RCI [53]), will be reported to provide an estimate of improvement/deterioration in each group that is not attributable to chance. Response will be defined as reliable improvement (i.e. improved more than the RCI), whilst also scoring at least 2 SD below the pretreatment mean. Partial response will be defined as fulfilling the RCI whilst scoring less than 2 SD below the pretreatment mean. Remission will be defined as scoring 6 or below on the QIDS-A17-SR [33].

Secondary outcomes will be analysed primarily according to ITT and with treatment termination as primary assessment point. Mean scores at termination will be compared across groups using analysis of covariance (ANCOVA) controlling for baseline scores.

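### The primary contrast is defined as a difference in change from baseline, but the non-inferiority rule is written on levels at termination, and the plan does not say which governs

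*Protocol article*

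**What the plan says.** Three statements in the protocol article make the primary contrast a difference in change.

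- Primary research question: "Is IPDT non-inferior to ICBT in reducing depressive symptoms from pre-treatment to end of treatment in adolescents".
- Outcomes {12}: "the difference between groups in estimated change in depressive severity from baseline to end of treatment (10 weeks".
- Statistical methods {20a}: "Differences in efficacy between conditions will be investigated by modelling interaction effects of group and time".

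The decision rule, later in the same paragraph of {20a}, is about levels. It takes "the upper 90% confidence interval of the estimated QIDS-A17-SR for the IPDT group at treatment termination" and declares non-inferiority if this limit lies under the ICBT point estimate with the margin added.

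On the margin, Sample size {14} says "A non-inferiority bound of *d* = 0.30 was set". It gives 80% power for 270 participants under two-level linear mixed models. It does not name the contrast that was powered or the SD that turns d into QIDS points.

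Baseline control is stated only for the secondary outcomes, which get an ANCOVA on baseline scores. On timing, Concealment mechanism {16b} says that "the randomization is conducted after completion of all baseline measures and final enrolment".

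**The concern.** The trial has a single yes/no primary verdict, and the article gives two contrasts from which it could be read. If the growth model lets the arms start from different fitted baselines, the difference in levels and the difference in change are different numbers with different standard errors. One can clear the 0.30 margin while the other does not, and nothing in the article says which then counts. The choice could be made after the data are seen. As far as the article states it, the primary verdict also has less baseline adjustment than the secondary outcomes.

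**Working it through.** **1. How the two contrasts relate.** Take differences as IPDT minus ICBT, with a higher QIDS-A17-SR score worse. With arm-specific intercepts:

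level difference at week 10 = change difference + fitted baseline difference.

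The two are equal only if the fitted baseline difference is zero, either by luck or because the model forces it. Below, the level rule is read as applying to the between-arm difference in levels.

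**2. The plan's own figure.** The simplest formula gives 2 × (1.645 + 0.842)² / 0.30² = 137.4, so 138 per arm and 276 in total at one-sided 5%, before attrition. Allowing for 20% attrition gives 346. A mixed model with the stated inputs gives 80% power for the change contrast at 270 if the baseline ICC is about 0.51–0.53 and d is in baseline SD. It does so equally at an ICC of about 0.21–0.26 with d in post-treatment SD. So 270 is compatible with a change contrast, but the stated inputs do not determine it.

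**3. Inputs for the comparison.**
- From the article: 135 per arm, 20% attrition, 20% intermittent missing data, variance ratio 0.75, margin d = 0.30, and one-sided 5% (implied by the 90% interval).
- Assumed: random intercept and slope, uncorrelated; variance ratio read as slope over residual variance with treatment time scaled 0 to 1; ICC from 0.3 to 0.6; 11 occasions. Table 1 of the article can be read as 12, which moves power by about one point.

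Power = Φ(0.30/SE − 1.645), with d in baseline SD. SEs are in baseline-SD units.

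| ICC | Level: SE, power | Change: SE, power | Common baseline: SE, power |
|---|---|---|---|
| 0.3 | 0.135, 71.8% | 0.146, 65.8% | 0.132, 73.6% |
| 0.4 | 0.133, 72.8% | 0.135, 71.7% | 0.125, 77.4% |
| 0.5 | 0.132, 73.7% | 0.124, 78.2% | 0.117, 82.2% |
| 0.6 | 0.130, 74.5% | 0.111, 85.3% | 0.107, 87.8% |

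Over variants of the dropout pattern and number of occasions, the ranges are about 71–75% (level), 64–86% (change) and 72–88% (common baseline). With d in post-treatment SD, the same model gives 83.7–86.3%, 81.0–92.4% and 87.6–94.1%.

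**4. How far apart the contrasts can be.** At ICC 0.5 the SE of the fitted baseline difference is about 0.10 SD, and 0.10/0.30 = 33% of the margin. Example: the estimated change difference is 0.03 SD and IPDT starts 0.10 SD higher, so the level difference is 0.13 SD.
- Change: upper limit 0.03 + 1.645 × 0.124 = 0.234, below 0.30, so non-inferior.
- Level: upper limit 0.13 + 1.645 × 0.132 = 0.347, above 0.30, so not shown.

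The two estimates correlate 0.63–0.79 over ICC 0.3–0.6. They give opposite verdicts in about 19–21% of trials when the treatments are equal, and in 21–29% when the true difference is 0.10 SD.

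**5. What chance imbalance does to each.** The SE of a raw baseline difference is √(4/270) = 0.122 SD. With equal SDs before and after treatment and pre–post correlation r, an imbalance of one SE shifts the level contrast by r × 0.122 and the change contrast by −(1 − r) × 0.122. These are +0.037 and −0.085 at r = 0.3, +0.061 and −0.061 at r = 0.5, and +0.085 and −0.037 at r = 0.7. Moving to unadjusted change does not remove the problem.

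**The case against.** The article does not say whether the growth model has a group effect at time 0. Without one, level and change already coincide, and fixed-effect terms are commonly left to an analysis plan. A free-intercept growth model is also a legitimate, standard choice. Randomisation keeps both contrasts unbiased for the same population difference, and chance imbalance is already inside each standard error.

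Most of this stands. Neither contrast is invalid, error control holds for whichever one is fixed in advance, and the common-baseline model is a gain in precision. It does not settle the point, because the article itself states both contrasts and no model term that would make them equal. That is a conflict in stated text and not an omitted detail.

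Two stronger readings are tempting, and the documents do not support them.

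- A reader might infer that the 80% power belongs to a contrast other than the one tested, and that the trial is underpowered. Sample size {14} names no contrast. If the change contrast was powered, the level test would have about 74% power with d in baseline SD but about 87–88% with d in post-treatment SD, so even the direction is unknown.
- A reader might infer that imbalance damages only the level rule, by the full 0.122 SD. Step 5 shows that it reaches both contrasts, and only in part.

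**Conclusion.** The point holds as an inconsistency that should be resolved before the analysis. The research question, the outcome definition and the interaction analysis describe a difference in change, while the decision rule describes levels at termination. With arm-specific intercepts, the two are separated by a fitted baseline difference with an SE of about 0.10 SD at ICC 0.5, and they disagree on the verdict in roughly one trial in five when the treatments are equal. Both are unbiased, and both were less precise than the common-baseline contrast at every ICC tried.

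The figures rest on the assumed ICC, time scale and variance structure, and those in the table on d being in baseline SD. Whether level or change has more power depends on inputs that the article does not give, so a shortfall against 80% is not shown.

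**What to change.** State one primary contrast and use it throughout.

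- Fit the growth model with a common baseline mean: keep baseline QIDS-A17-SR in the outcome vector, include no group effect at time 0, and retain group-by-time. This is valid because all baseline measures precede randomisation.
- Base the decision on the 90% CI of the between-group difference at end of treatment from that model, with non-inferiority when its upper limit is below the margin. Level and change differences are then the same number.
- Name the SD that converts d = 0.30 into QIDS points.
- Confirm that the power in Sample size {14} refers to this contrast, and give the ICC and time scale used.

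The cost is wording, plus a rerun of the power calculation if it was made for another contrast. No new data or participants are needed.

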### Plans for assessment and collection of outcomes {18a}

Data will be collected at baseline, weekly during treatment, at treatment termination as well as at three follow-up occasions (1, 6 and 12 months after termination).

All instruments consist of online-administered self-report questionnaires with established validity and reliability. Four self-rating scales will be administered weekly to track the primary outcome and possible mediators, whilst other questionnaires will be solely administered at baseline, termination and follow-up (see Table 1 for the measurement timeline).

**Table 1 Tab1:** Schedule of enrolment, interventions and assessments

Activity/assessment	Online screening/baseline	Telephone interview	Post-randomization		Follow-up		
	***− t***_**1**_	***t***_**0**_	***t***_**1–10**_ (weekly)	***t***_**11**_ (post)	***f***_**1**_	***f***_**2**_	***f***_**3**_
Informed consent	X						
Demographic data	X						
ICBT/IPDT			X				
M.I.N.I 7.0		X					
C-SSRS		X					
DSRFI		X					
Treatment Expectancy^a^	X		X				
QIDS-A17-SR	X		X	X	X	X	X
SAI-C/SAI-T			X				
GAD-7	X			X	X	X	X
SCS-SF	X			X			
PID-5-BF	X						
TiC-P	X						X
ERSQ-27	X			X			
ERSQ-9			X				
ECR-RS	X						
OPD-SQS	X						
Termination form				X			

*M.I.N.I* Mini International Neuropsychiatric Interview, *C-SSRS* Columbia Suicide Severity Rating Scale, *DSRFI* Depression-specific reflective functioning interview, *QIDS-A17-*SR Quick Inventory of Depressive Symptomatology in Adolescents, *SAI-C* Session Alliance Inventory – Client version, *SAI-T* Session Alliance Inventory – Therapist version, *GAD-7* Generalized Anxiety Disorder -7, *SCS-SF* Self-Compassion Scale short-form, *PID-5-BF* The Personality Inventory for DSM Short Form, *TiC-P* Trimbos and Institute of Medical Technology Assessment Cost Questionnaire for Psychiatry, *ERSQ* Emotion Regulation Skills Questionnaire (27/9 items), *ECR-RS* Experiences in Close Relationships - Relationship Structure*, OPD-SQS* OPD-Structure Questionnaire short version. *F*_1_: 1 month, *F*_2_: 6 months; *F*_3_: 12 months

^a^“How much do you expect your depression to improve as a result of treatment?” on a 7-point Likert scale ranging from “− 3” (I expect to feel much worse) to “3” (I expect to feel much better)

#### Primary outcome

The primary outcome will be depressive symtoms, measured with the Quick Inventory of Depressive Symptomatology in Adolescents Self-Rated (QIDS-A17-SR [32]). The QIDS-A17-SR is a self-rated measure which has shown reliability and validity in previous studies amongst both adults and adolescents (e.g. [32–34]). Its brevity allows for weekly symptom ratings, which is needed for more sophisticated longitudinal statistical analyses. Assessments will be made via Internet-delivered self-rating forms pre-treatment, weekly during treatment, post-treatment and during follow-ups. The adolescent version is identical to the adult version with the addition of simultaneously assessing increased irritability as a symptom of adolescent depression.

#### Secondary outcomes

All secondary outcome measures have shown reliability and validity in previous studies. The secondary outcome measure for anxiety symptoms will be the Generalized Anxiety Disorder 7-item scale (GAD-7 [35]). The Emotion Regulation Skills Questionnaire (ERSQ [36]) will be employed to evaluate whether or not treatments are associated with participants’ enhanced capacity for emotion regulation. To assess their capacity for self-compassion, we will apply the Self-Compassion Scale Short Form (SCS-SF [37]).

#### Additional instruments

This trial also encompasses a range of measures to be analysed in additional papers following the main outcome paper. We will employ a range of measures to assess possible moderators for treatment effects: attachment, measured with the Experience in Close Relationships – Relationships Structure (ECR-RS [38]); self compassion, measured with the SCS-SF [37]; personality structure, measured with the OPD-Structure Questionnaire Short form (OPD-SQS [39]); and personality problems, measured with the Personality Inventory for DSM short form (PID-5-BF [40, 41]), all of which will be assessed at baseline.

We will also conduct a short interview at baseline to assess depression-specific reflective functioning ([name], [name], [name] & [name]: Depression-specific Reflective Functioning Interview for adolescents, Unpublished), which seems to work as a predictor for both the therapeutic alliance and outcome in standard face-to-face psychotherapy targeted at depression [42].

Possible outcome mediators will be assessed with the following instruments administered weekly during treatment: a nine-item version of the Emotion Regulations Skills Questionnaire (ERSQ-9 [36]), the Session Alliance Inventory (SAI [43]) measuring treatment alliance as experienced by both therapists and participants, and the single-item expectancy measure (adapted from Moras and Jones [44] and Connolly Gibbons et al. [45]). The SAI and expectancy measures will be filled out by participants and therapists alike.

Cost-effectiveness will be assessed with the Trimbos and Institute of Medical Technology Assessment Cost Questionnaire for Psychiatry (TIC-P [46]) at baseline and at the 12-month follow-up. Following recommendations for assessing cost-effectiveness in adolescents’ treatments [47], solely the sections of the TIC-P regarding healthcare use will be administered.

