### Objectives {7}

This study protocol describes a non-inferiority RCT that will evaluate the efficacy of therapist-assisted ICBT and IPDT for adolescent depression. The study has been preceded by a pilot RCT (*n* = 76) that investigated the efficacy of a novel IPDT treatment for depressed adolescents compared to control condition consisting of weekly symptom follow-up and online supportive contact [23]. The pilot trial showed clinically and statistically significant effects of IPDT compared to control thereby depicting the treatment’s strong acceptability and feasibility. Answering to the need of increased accessibility to digital health interventions, the main goal of the planned study is to further compare the IPDT treatment for depressed adolescents to an established evidence-based treatment (ICBT) in terms of efficacy, cost-effectiveness and factors that affect differential suitability. The primary aim is to examine whether or not therapist-assisted IPDT is non-inferior to therapist-assisted ICBT in treating depression.

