### Intervention description {11a}

Both interventions consist of eight therapist-supported self-help modules delivered over 10 weeks on a secure online platform [25]. The modules contain text and videos followed by assignments the patients send to their therapist, receiving feedback within a few days. In addition, participants in both arms of the study will receive 30 min of weekly therapist support via text chat, which was found to be an important ingredient in the empirically supported version of ICBT for adolescents [9, 10]. A guidance protocol (available upon request) has been developed for contact with participants, message frequency and support for handling participants who do not follow their treatment protocols. This guidance protocol is being applied to both treatments to ensure the amount of contact and guidance is comparable in both interventions and further, to ensure the differences amongst the treatments solely regard content and not format.

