### Relevant concomitant care permitted or prohibited during the trial {11d}

No concurrent psychological treatment is permitted in order to be included in the trial. Participants are informed that they should not enter concurrent treatment during the treatment phase of the trial. However, if they do so, this is not cause for exclusion from the trial. Participants are asked at post-treatment and all follow-up about any concurrent treatments and this is carefully recorded. Psychotropic medications during the period of treatment are permitted, granted that treatment dose have been stable for at least 1 month prior to enrollment, with no planned dose adjustments during the trial.

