## Discussion

The need to develop early, brief, focused and effective interventions for depressed adolescents is urgent. Internet-based interventions are designed to reach, amongst others, people who do not access youth mental health services, or seek or receive traditional psychotherapy. One aim is to increase their access to psychological treatments, as well as increase such treatments’ cost effectiveness. Making treatment more easily accessible might also propose major health benefits because accessible treatment enables adolescents to apply for and receive treatment at an earlier stage of a psychiatric disorder. Internet-based interventions also have the potential to reach patients who would otherwise avoid seeking treatment due to social stigma [55]. It has been suggested that Internet-delivered treatment might also be useful for reaching adolescents with more severe symptoms who are reluctant to seek care on their own [56].

Empirical support has already been established for ICBT and the ICBT protocol used in the present study achieved clinical significant change in 46% of cases [10]. Preliminary results from the pilot IPDT trial suggest similar response rates. The trial is based on an extensive power analysis, based on data from two previous trials as well as a pilot trial, and especially taking the specific statistical analyses that are planned (i.e. multilevel modelling) into account. This trial is designed to investigate whether or not IPDT is non-inferior to ICBT with regard to depressive symptoms as well as determine whether or not the treatments are comparable regarding cost-effectiveness, thereby increasing treatment alternatives. Several secondary outcome measures are also assessed, in order to investigate possible differential effects of the treatments. Furthermore, we hope that the future moderator analyses will provide information regarding which adolescents will benefit the most from ICBT and IPDT, whilst mediator analyses will shed light on possible different treatment trajectories and processes.

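### The healthcare-use questionnaire is given only before randomisation and 12 months after termination, so costs during the 10 treatment weeks may go unmeasured and the cost-effectiveness comparison is weakened

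*Protocol article*

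**What the plan says.** The section Additional instruments names the TiC-P as the instrument for cost-effectiveness, times it "at baseline and at the 12-month follow-up", and limits its content: "solely the sections of the TIC-P regarding healthcare use will be administered". Table 1, under Plans for assessment and collection of outcomes {18a}, agrees. The TiC-P is marked at online screening/baseline and at the third follow-up, and is blank at post-treatment and at the 1- and 6-month follow-ups. The same section describes the follow-ups as "three follow-up occasions (1, 6 and 12 months after termination", so they are counted from the end of treatment, not from randomisation.

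The aim that this instrument serves appears in several places. Objectives {7} describes the main goal as comparing the treatments "in terms of efficacy, cost-effectiveness and factors that affect differential suitability". The Discussion says the trial is designed to "determine whether or not the treatments are comparable regarding cost-effectiveness". The list of secondary research questions leaves the analysis to a later paper.

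Two other sources bear on resource use. Relevant concomitant care {11d} states: "Participants are asked at post-treatment and all follow-up about any concurrent treatments and this is carefully recorded". Strategies to improve adherence {11c} says that participants' activity in the programme is recorded automatically on the platform.

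**The concern.** A cost comparison between randomised arms normally runs from randomisation to the end of the costing window. Here the one instrument named for costing is completed once before randomisation and once more than a year after treatment starts. Unless the later form asks about a period longer than 12 months, it cannot reach the treatment phase, and the baseline form cannot cover it either.

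An analysis plan can choose a costing window, but it cannot recover healthcare use that was never asked about. The article defers the analysis to a further paper, yet the data have to be collected during this trial. The schedule also leaves a single point of failure: a participant who misses the 12-month visit contributes no TiC-P data after randomisation.

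**Working it through.** The plan gives no figure for cost coverage, so there is none to reproduce. The check is arithmetic on the timeline.

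**Inputs**
- Treatment: "eight therapist-supported self-help modules delivered over 10 weeks" (Intervention description {11a}).
- Treatment starts the day after randomisation (Implementation {16c}), and baseline measures are complete before randomisation (Concealment mechanism {16b}).
- Last TiC-P: 12 months after termination ({18a} and Table 1).
- Recall period of the TiC-P: not stated. Assumed range: 1 to 12 months, plus the recall needed to reach the start of treatment.

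**Span to be costed**
- Weeks per month = 365.25 / 12 / 7 = 4.348.
- Follow-up year = 12 × 4.348 = 52.2 weeks.
- Span = 10 + 52.2 = 62.2 weeks, and 62.2 / 4.348 = 14.3 months.
- Treatment phase = 10 / 4.348 = 2.3 months, and 10 / 62.2 = 16% of the span.

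**Coverage by the form at the 12-month visit, counting back from that visit**

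Weeks covered = recall in months × 4.348, up to 62.2. Treatment weeks covered = weeks covered − 52.2, or 0 if that is negative.

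| Recall | Weeks covered | Share of 62.2 weeks | Treatment weeks covered | Weeks not covered |
|---|---|---|---|---|
| 1 month | 4.3 | 7% | 0 | 57.8 |
| 3 months | 13.0 | 21% | 0 | 49.1 |
| 6 months | 26.1 | 42% | 0 | 36.1 |
| 12 months | 52.2 | 84% | 0 | 10.0 |
| 14.3 months | 62.2 | 100% | 10 | 0 |

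With a 12-month recall, the part not covered is exactly the treatment period. With a 6-month recall, half of the follow-up year is lost as well. Full coverage from this one form needs a recall of about 14.3 months.

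**After adding forms**
- Post-treatment form reaching back to baseline (10 weeks of the span) plus a 12-month recall at the last visit (52.2 weeks) = 62.2 weeks, the full span.
- If the recall at the last visit is 6 months: post-treatment (10) + 6-month follow-up (26.1) + last visit (26.1) = 62.2 weeks, again the full span.
- If the recall at both follow-ups stays at 3 months: 10 + 13.0 + 13.0 = 36.1 weeks (with unrounded terms), or 58%. The added forms therefore close the gap only if each asks about use since the previous form.

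**The case against.** A reader might infer that the cost-effectiveness aim cannot be answered at all. The documents do not support that. With a 12-month recall, healthcare costs over the whole year after termination can still be compared between arms. Concurrent treatments are asked about at post-treatment and every follow-up, and recorded treatments can be costed to some degree. Use of the programme itself is logged. This part of the objection stands. What remains is that the article does not say that the concurrent-treatment question counts contacts, extends to other healthcare or feeds the costing, and the platform logs do not see care outside the trial.

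A reader might also conclude that coverage of the treatment phase is simply zero. That depends on a recall of 12 months or less. An article may leave the recall period to the full protocol or a health-economic plan, so its absence here is not itself a fault. A form asking about use since baseline would cover everything on paper. It would do so, however, through one self-report spanning more than 14 months.

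A third inference would be that any difference in cost is most likely to arise during treatment. Nothing in the article shows this. Participants are told not to start other treatment in that phase, psychotropic medication must be stable at entry, and contact is matched between arms. The article does provide for referral to psychiatric care if a participant deteriorates severely ({11b}), so outside care in those weeks is foreseen, but its amount and its difference between arms are unknown.

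Finally, the primary aim is non-inferiority on depressive symptoms, and this point touches neither the primary nor the listed secondary outcomes. That is correct and limits its weight.

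**Conclusion.** The point holds as a limited weakness in data collection for a secondary aim. No systematic healthcare-use form falls between randomisation and a visit about 14.3 months after treatment starts. At a recall of 12 months or less, all 10 treatment weeks are missed: 16% of the span at 12 months, rising to 58%, 79% and 93% not covered at 6, 3 and 1 months (100% minus the shares in the table). At a longer recall, everything rests on a single long report. Total costs from randomisation to the 12-month visit may therefore be incomplete, and the comparison is weakened, not ruled out.

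The size depends on the unstated recall period and on how much detail the concurrent-treatment record holds. If that record proves to be a full count of healthcare contacts, most of the gap closes. The direction of any resulting bias in the cost difference cannot be judged from the article.

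**What to change.** Add the TiC-P healthcare-use section to the online battery at post-treatment, asking about use since baseline. If the recall at the 12-month visit is shorter than 12 months, add it at the 6-month follow-up too, with each form asking about use since the previous one. If that recall is a full 12 months, the post-treatment form alone is enough. State the recall period and the costing window, and say how the concurrent-treatment record will be used.

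For participants already past those assessments, either use the concurrent-treatment record for the missing weeks or limit the costing window to the period actually covered, and report which was done.

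The cost is small: probably a few more minutes at assessments that already take place online with reminders (a judgement, since the article gives no completion time), and an ethics notification. Data would be more complete for later participants than for earlier ones, which the cost paper should describe.
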